### Hypotheses and study endpoints

#### Primary aims

We hypothesize 16 weeks of ingesting a synbiotic preparation compared to placebo will result in statistically significant improvements (within-group and between-group) in:4-m gait speedStanding balanceRepeated chair risesTimed up and go Handgrip strength

#### Secondary aims

We hypothesize 16 weeks of ingesting a synbiotic preparation compared to placebo will result in statistically significant improvements (within-group and between-group) in:(6)Muscle mass and body composition (LBM, ALM, total and regional body FM and FFM)(7)Muscle quality (CSA, MT, EI, FL, and PA of *Rectus femoris* and *Vastus intermedius* muscles)(8)Fecal microbiota composition and diversity(9)Untargeted fecal and serum metabolomics

#### Safety aims

We hypothesize synbiotic administration will be safe and well-tolerated as defined by the absence of:(10)Changes (outside normal variation) in CBC elicited after baseline and through week 16(11)Changes (outside normal variation) in CMP elicited after baseline and through week 16(12)AEs elicited after baseline and through week 20(13)SAEs until study completion

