### Safety outcome measures

Serum and plasma samples will be analyzed by an external commercial pathology facility to determine changes (outside normal variation) in clinical chemistry (Comprehensive Metabolic Panel [CMP]) and clinical hematology markers (Complete Blood Count [CBC]) elicited after baseline and through week 16. Adverse events (AEs) and serious adverse events (SAEs) will be assessed and recorded from baseline through week 20.

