### Relationship to study intervention

The principal investigator (PI) will assess all AEs and SAEs to determine whether there is any potential relationship to the study intervention. The relationship will be assessed as either “related” or “unrelated” as below:*Related*: There is a reasonable possibility that the study intervention caused the AE or SAE, or there appears to be a temporal relationship between the administration of the study intervention and the event.*Unrelated*: There does not seem to be a reasonable possibility that the administration of the study intervention caused the AE or SAE, there does not appear to be a temporal relationship between the study intervention and event onset, or there has been an alternate etiology established that explains the event.

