### AE and SAE reporting

All AEs and SAEs will be captured on the *adverse events log*.

The PI will be responsible for notifying the approving HREC of any SAE, independent of the relatedness to the study, within 7 calendar days upon initial receipt of the information. If the SAE is considered as related to the IP, a report must follow within 7 days of learning about the SAE.

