### Period for collecting AEs/SAEs

The period for collecting AEs and SAEs (“active collection period”) for each participant is as follows:AEs: From informed consent until the end of study involvement (week 20).SAEs: From informed consent until study completion.

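### Safety is defined as having no adverse events at all, which is almost certain to fail at plausible event risks, and the event-recording rules conflict

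*Protocol article*

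**What the plan says.** **The criterion.** Under Safety aims the hypothesis is: "We hypothesize synbiotic administration will be safe and well-tolerated as defined by the absence of" four items. They are blood-count changes and metabolic-panel changes (the latter worded "Changes (outside normal variation) in CMP elicited after baseline and through week 16"), then "AEs elicited after baseline and through week 20" and "SAEs until study completion". The primary and secondary hypotheses directly above name placebo as comparator; the safety hypothesis does not. The Risk–benefit analysis section says that side effects can occur and are mostly minor, self-resolving gut symptoms.

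**Which events are recorded.** Safety reporting first defines an AE without requiring a causal link, then describes it as something that appears associated with the product. It goes on to say that the events judged related to taking part are the ones collected, recorded and sent to the ethics committee. AE and SAE reporting says "All AEs and SAEs will be captured on the" log, and that any SAE is notified whatever its relatedness.

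**When.** Safety outcome measures says AEs and SAEs "will be assessed and recorded from baseline through week 20". Period for collecting AEs/SAEs gives, for AEs, "From informed consent until the end of study involvement (week 20"), and for SAEs consent to study completion.

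**Relatedness.** An event is *related* if there is a reasonable possibility of causation, or if "there appears to be a temporal relationship between the administration of the study intervention and the event". It is *unrelated* if, among other alternatives, another cause has been established.

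**The concern.** A hypothesis of zero events is refuted by one cold in one synbiotic participant. It counts background illness against the product and does not use the placebo arm, which is there to separate the two. A harmless product would then be declared not safe, or the authors would have to set aside their own definition after seeing the data.

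The recording rules decide what the counts mean. If only events judged related reached the log, the counts would depend on that judgement, and the absence of AEs as the Safety aims word it could not be checked. If relatedness can be read two ways for one event, a table of related events is not reproducible.

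**Working it through.** The article states no AE rate, safety margin or safety power, so there is no figure of its own to reproduce. The check is whether the criterion could be met.

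**Inputs.** n = 37 on synbiotic (Study participants). With the roughly 30% dropout in Statistical analyses and power, 37 × 0.7 ≈ 26. The per-person risk p of at least one AE over 20 weeks is assumed, and a range is shown.

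**Chance of no AE in the synbiotic arm** = (1 − p)^n.

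| Assumed p | n = 37 | n = 26 |
|---|---|---|
| 1% | 0.69 | 0.77 |
| 2% | 0.47 | 0.59 |
| 5% | 0.15 | 0.26 |
| 10% | 0.020 | 0.065 |
| 20% | 0.0003 | 0.003 |

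The formula gives everyone the same risk. If risks vary around the same mean, the chance is lower, because the product of the (1 − p) terms is then smaller.

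**Risk needed to pass.** For a 50% chance of zero events, p = 1 − 0.5^(1/37) = 1.9%. For an 80% chance, p = 1 − 0.8^(1/37) = 0.6%.

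**What a pass would show.** With 0 of 37, the exact one-sided 95% upper limit is 1 − 0.05^(1/37) = 7.8%. With 0 of 26 it is 1 − 0.05^(1/26) = 10.9%.

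**Recording rules side by side.**

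| Question | One section | Another section |
|---|---|---|
| Which events | Events judged related (Safety reporting) | All AEs and SAEs; any SAE notified (AE and SAE reporting) |
| Start | Baseline (Safety outcome measures) | Informed consent (Period for collecting AEs/SAEs) |
| End, SAEs | Week 20 (Safety outcome measures) | Study completion (Period for collecting AEs/SAEs; Safety aims) |
| On-product event with an established other cause | *Related*, by timing | *Unrelated*, by the other cause |

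If the Safety reporting sentence is taken only as an ethics-reporting rule, it still disagrees with the requirement to notify every SAE. The two start points are at most two weeks apart, the maximum screening period under Study duration.

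**The case against.** Several stronger readings are tempting, and the documents do not support them.

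- **That no trial could meet the criterion.** Zero events is possible: 15% at a 5% risk and 69% at 1%. The supportable statement is that failure is almost certain at the risks one would expect for all-cause events at ages 60 to 85.
- **That any out-of-range laboratory value fails it.** The text speaks of changes beyond normal variation, gives no threshold and could be meant at group level. A calculation from 95% reference ranges would test a rule that the article does not state, so none is used here.
- **That placebo plays no part in the analysis of safety.** The statistics section applies a linear model to the study hypotheses, comparing the two groups, and does not exclude safety. That stands, but a linear model comparing groups cannot test an absence of events.
- **That the trial cannot answer its safety aim, or that only related events are logged.** The aim is to assess safety and tolerability, and the data are collected in both arms. The log section captures everything, and the relatedness section has the investigator assess all events. These favour full capture; the conflicting sentence is still there.
- **That the start-date gap biases the comparison.** It falls before any product is taken, and collecting from consent is compatible with counting from baseline. Only the statement that recording starts at baseline conflicts.
- **That an event is logged in both classes.** The section requires one or the other, and site staff are blinded. The weakness is that the definitions do not determine which class applies.

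It is also fair to say that tables and intervals usually belong in the analysis plan, which is not shown. The point does not rest on their absence: the zero-event definition is stated in the article and would remain.

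**Conclusion.** The point holds. The stated definition of safe and well tolerated gives a 15%, 2% or 0.03% chance of success at assumed risks of 5%, 10% or 20%, and needs a risk of 1.9% or less for an even chance. The outcome says little about the product, because background events count and placebo is not part of the definition. A pass would be weak evidence too, with an upper limit of 7.8%. The AE item alone carries this. The risks are assumptions, but the article's own expectation of gut symptoms makes the lowest ones implausible.

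The conflicts over which events are recorded, the recording windows and relatedness stand in the current text. Their effect on the arm comparison is probably modest if the log holds all events. The efficacy result does not depend on any of this. The change is worth making because it is cheap and improves what can be concluded on safety.

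**What to change.** - **Criterion.** In the Safety aims, replace the zero-event definition with a between-arm comparison of the proportions with any AE, any SAE and any gastrointestinal AE, each as a risk difference with 95% CI. Add between-arm comparisons of blood-count and metabolic-panel changes, and of the gastrointestinal and constipation scales listed in the Fig. 1 legend.
- **Recording.** Reconcile Safety reporting with AE and SAE reporting so that every event is recorded whatever its cause, with one AE definition and relatedness tabulated separately.
- **Windows.** Reconcile Safety outcome measures with Period for collecting AEs/SAEs on the start and on the SAE end. Keep post-baseline events as the comparison set, so that pre-product events are not mixed in.
- **Relatedness.** Make the two classes mutually exclusive.

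The cost is rewording and a few more tables, with no new participants or visits. The comparison will be imprecise and should be presented as estimation. At an assumed 20% in each arm, the 95% half-width is 1.96 × √(2 × 0.2 × 0.8 / 37) ≈ 0.18, or 18 percentage points.

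Recruitment began in November 2022 and was expected to reach its target in April 2024. The sponsor should therefore confirm now that the log already holds all events and not only those judged related.

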### Risk–benefit analysis

All participants will be monitored and questioned for side effects. Both probiotics and prebiotics are safe for the majority of the population, but side effects can occur. Side effects of probiotics and prebiotics are usually minor and consist of self-limited gastrointestinal symptoms, such as a temporary increase in gas, mild abdominal discomfort, bloating, diarrhea, and constipation. Side effects can vary from mild to very serious and may vary from person to person. In some cases, these effects might be long-lasting, or permanent, and may even be life-threatening.

Food allergy symptoms (such as tingling or itching in the mouth; hives; swelling of the lips, tongue or other body parts; abdominal pain; diarrhea, or lightheadedness) may be experienced within a few minutes to 2 h after consuming the probiotic and prebiotic supplement if the participant is allergic to any of its ingredients.

Synbiotics (products containing a mixture of probiotics and prebiotics) are generally considered safe, particularly in healthy people; however, there are some risks. These risks are increased in participants who have compromised immune systems or have other serious medical conditions. Possible harmful effects can include developing infections or antibiotic resistance, or the production of harmful by-products from microorganisms contained in the synbiotic.

The risks of adverse events associated with this study are minimal, and any adverse events will be recorded and managed following Good Clinical Practice (GCP) guidelines and legal requirements. However, this study will provide important outcomes regarding the potential benefits of synbiotic consumption on physical function, strength and body composition, which may provide supporting evidence for the use of synbiotics as a cost-effective supplement for older individuals. Participants will be fully informed about the risks associated with the study before providing informed consent and will have the right to withdraw at any time. This will be explained in the ICF document and verbally during the screening process.

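### The safety aim defines safe and well tolerated as zero events on synbiotic, without reference to the placebo arm, so ordinary background events would probably make an inert product fail it

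*Protocol article*

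**What the plan says.** Under Hypotheses and study endpoints, the Safety aims hypothesise that "synbiotic administration will be safe and well-tolerated as defined by the absence of" four items. They are "Changes (outside normal variation) in CBC elicited after baseline and through week 16", the same for the metabolic panel, "AEs elicited after baseline and through week 20", and "SAEs until study completion". No rate, margin or comparator is attached.

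The efficacy hypotheses in the same section are worded differently: "We hypothesize 16 weeks of ingesting a synbiotic preparation compared to placebo will result in statistically significant improvements". The secondary hypotheses use the same placebo-referenced form. Only the safety hypothesis leaves placebo out.

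Safety outcome measures says samples will be analysed "to determine changes (outside normal variation) in clinical chemistry (Comprehensive Metabolic Panel [CMP]) and clinical hematology markers" and that AEs and SAEs will be recorded to week 20. It states no between-arm comparison either.

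Three other sections bear on the definition:

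- Risk–benefit analysis: "Side effects of probiotics and prebiotics are usually minor and consist of self-limited gastrointestinal symptoms", with gas, bloating, diarrhoea and constipation among the examples.
- Safety reporting: an AE is any untoward occurrence, need not be causal, and may be an abnormal laboratory finding.
- Relationship to study intervention: a temporal relationship alone is enough to class an event as related.

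**The concern.** The trial has a blinded 1:1 placebo arm, which is what separates product effects from the background of symptoms, illness and laboratory fluctuation in people aged 60 to 85 followed for 20 weeks. The safety definition does not use it. It asks whether anything happened on synbiotic, not whether more happened than on placebo.

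Two errors can follow. If both arms have the same ordinary AE rate, the stated hypothesis is still rejected as soon as one synbiotic participant has an AE. If the team then sets the definition aside because it is unworkable, the safety conclusion rests on a criterion chosen after the data were seen. In the other direction, the SAE item counts as met when no SAE occurs, although 37 people cannot exclude a rate that would matter.

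Safety is one of the three stated aims, and the Discussion expects the project to describe safety and tolerability.

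**Working it through.** **Plan's own figure.** None. The article attaches no rate, margin, alpha or power to the safety aim, so there is nothing to reproduce.

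**Inputs**

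- Synbiotic participants: 37 (Abstract, Methods).
- Dropout: about 30% (Statistical analyses and power), so 37 × 0.70 = 25.9, about 26 completers.
- Per-person probability p of at least one AE over 20 weeks: not given, so assumed over a range.

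**Chance of meeting the AE item.** With independent participants, P(no participant with an AE) = (1 − p)^n.

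| Assumed p | n = 37 | n = 26 |
|---|---|---|
| 1% | 69% | 77% |
| 2% | 47% | 59% |
| 5% | 15% | 26% |
| 10% | 2.0% | 6.5% |
| 20% | 0.03% | 0.3% |

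For example, 0.90^37 = 0.020 and 0.90^26 = 0.065. All four items must be absent, so the chance of meeting the whole definition cannot exceed the chance of meeting this one.

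**Break-even rate.** For a 50% chance of meeting the AE item, p may be at most 1 − 0.5^(1/37) = 1.9% with 37, or 1 − 0.5^(1/26) = 2.6% with 26.

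**SAE item.** With 0 SAEs in 37, the one-sided 95% upper limit is 1 − 0.05^(1/37) = 7.8%. The item is met, yet a true risk of about 1 in 13 is not excluded.

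**Laboratory item.** No single figure can be given, because normal variation is not defined. Assume 20 independent analytes, one visit and a flag rate q per analyte. Then P(no flag in 37) = (1 − q)^(20 × 37). This is about 3 × 10^-17 at q = 5%, 0.06% at q = 1% and 48% at q = 0.1%. The answer depends entirely on a definition the article does not supply.

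**What a between-arm comparison could show.** At an assumed 20% in each arm, the 95% half-width of the risk difference is 1.96 × √(2 × 0.20 × 0.80 / 37) = 0.182, about ±18 points. The power of a two-sided 5% test of 20% against 40% is Φ[(0.20 × √37 − 1.96 × √(2 × 0.30 × 0.70)) / √(0.20 × 0.80 + 0.40 × 0.60)] = Φ(−0.085) = 47%. The data suit estimation better than testing.

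**The case against.** **The analysis section may already compare the arms.** The statistical section says the study hypotheses will be tested between intervention and placebo with a hierarchical linear model, and the safety items are numbered as part of the same list of hypotheses. A reader might infer that the plan contains no placebo comparison for safety at all. The text does not support that: the general sentence could nominally cover blood count and metabolic panel values, and safety data are collected in both arms. What stands is narrower. The sentence does not name safety, and a linear model does not test an absence. The stated primary analysis is of participants who complete the trial. Since participants may be withdrawn for a related AE, that set can lose the people who matter most for safety.

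**The hypothesis may mean product-related events only.** The word elicited, used for the laboratory and AE items, can be read as caused by the product. Safety reporting also describes an AE as appearing to be associated with the product, and refers to events deemed related. This reading lowers p and moves up the table. It does not remove the difficulty: timing alone makes an event related, gastrointestinal effects of the product are expected, and the SAE item does not use the word.

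**The outcome depends on rates the article does not give.** This is correct. A reader might infer that the aim fails almost whatever the product does. At a 2% risk the AE item is met about half the time, so that reading goes too far. Nor can the laboratory item be called practically impossible to meet. That holds only if a change outside normal variation means any value outside a 95% reference interval, which the article does not say.

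**A full analysis plan may add a safety comparison.** It may. But the article does not leave this open: it states a definition, and a different rule elsewhere would have to be reconciled with it.

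**Conclusion.** The point holds as a fault in the stated definition. Safe and well tolerated is fixed as complete absence of events on synbiotic, without reference to placebo, and this conflicts with the side effects the article expects and with its own AE and relatedness definitions.

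The size depends on the assumed AE risk. Above roughly 2 to 3% per person over 20 weeks, failure of the AE item is more likely than not. At 10% the item is met 2.0% of the time (6.5% among completers). Such risks are plausible for this age group under so broad an AE definition, but that is a judgement and not a figure from the article. The calculation also assumes independent participants. No size is claimed for the laboratory item.

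The efficacy analysis and sample size are unaffected. What is affected is whether the safety aim can yield an interpretable conclusion. The definition should be changed before unblinding.

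**What to change.** Replace the zero-event definition in Safety aims with a synbiotic-versus-placebo comparison in all randomised participants who took at least one sachet, analysed as a safety set separate from the completers and the adherent subset.

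Report per-arm counts and the synbiotic-minus-placebo risk difference with a 95% confidence interval for participants with at least one:

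- AE;
- gastrointestinal AE;
- SAE;
- new blood count or metabolic panel abnormality, with a stated definition of abnormality in place of normal variation.

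Word the conclusion by the upper confidence limit: no excess over placebo larger than that value. State whether the AE comparison covers all AEs or only related ones, and reconcile the two descriptions of an AE in Safety reporting.

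The cost is revised wording and a few tables from data already scheduled in both arms. The downside is a more modest claim: at an assumed 20% AE rate the interval is about ±18 points, so the trial can describe safety against placebo but cannot exclude a sizeable excess.

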### Statistical analyses and power

This estimated sample size for the main outcome measures of physical performance was based on an assumed correlation of 0.7 between the pre- and post-intervention outcome measures, and an effect size of Cohen’s *d* = 1.2 for gait speed based on data from Román et al. [29] that examined the effects of a multi-strain probiotic on gait speed and the TUG test in a study cohort of 35 (17 and 18 in treatment and placebo groups, respectively). To have a power of 80% and a significance level of 5%, our study aims to enrol an estimated sample size of 74 participants (37 per group), taking into account a conservative ~ 30% dropout rate.

The study hypotheses will be addressed using a hierarchical linear model analysis to test for significant differences between the two comparative groups (intervention and placebo) over time. A primary intention to treat (ITT) analysis will be conducted on all the participants who complete the trial. Additionally, a secondary analysis will be carried out to include only participants who consumed ≥ 90% of their supplement over the course of the intervention period. Between-group comparisons will be made using linear models and statistical significance set at *p* < 0.05. Where there are significant group xtime interactions, planned contrasts will compare changes from baseline under each intervention. Similar tests will be performed for the secondary hypotheses, using appropriate transformations if these measures exhibit non-normal distributions across time points. This analysis will allow for the control of any baseline group differences and to test for moderation effects in terms of these variables over time. Analysis of microbial community composition will be conducted using Phyloseq and vegan package in R version 3.6.1 as per protocol.

Wilcoxon’s signed-rank test, Spearman’s rank correlation (p), Pearson’s correlation (r), multiple linear regression, and/or linear mixed models will be used to examine associations and appropriate comparisons depending on the distributions of the variables. Relationships between markers of functional performance, ordinations of stool microbiota composition, and stool/plasma metabolites will also be assessed using the Structural Equation Model to enable causal assumptions to be interpreted between variables to ensure these relationships are not “coincidental” and linear mixed models. All mixed models will include the subject as a random factor and time as a continuous covariate. Backward stepwise regression will be used to identify the strongest predictors of changes in aspects of functional performance. The false discovery rate for all tests will be controlled by adjusting *P* values using the Benjamini–Hochberg procedure. Adjusted *P* values will be presented as *Q* values. Statistical analyses will be completed using SPSS v.26. 11.2.2

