Few studies have explored the gut-muscle axis in humans, especially within the elderly. Bacterial taxa such as *Enterobacteriaceae*, *Bacteroides*, and *Prevotella*, have been correlated with measures of gait speed [15]. A 2022 study found that the diversity and composition of gut microbiota in community-dwelling older adults was associated with sarcopenia [19]. Claesson et al. demonstrated that physical performance was inversely related to species richness of the fecal microbiota of 178 older subjects [20]. Analysis of data from 371 ELDERMET cohort subjects revealed an association between the presence of frailty in community-dwelling elderly individuals and comparable gut microbiome profiles of nursing home residents [21]. Furthermore, an adequate representation of *Bifidobacterium* has shown to be fundamental for the production of butyrate [22], a short-chain fatty acid (SCFA) with important anti-inflammatory and pro-anabolic activities involved in the gut-muscle axis. Treatment with butyrate appears to protect against age-related muscle atrophy [23], which supports the idea that pre- and/or probiotic supplementation, known to increase the abundance of *Bifidobacterium* and butyrate producers in older individuals [24, 25], may protect against physical performance deficits with aging [16]. Despite this, there is a scarcity of research evaluating the effect of gut-modulating supplements in older populations. A recent systematic review found no clear evidence of benefit in physical performance in 5 studies evaluating the use of pre-, pro-, or synbiotics in older adults [26]. Notwithstanding, 12 weeks of consuming a synbiotic increased SCFA production compared with a placebo in elderly individuals in a 2013 study [27]. In a more recent trial, 13 weeks of consuming a prebiotic improved handgrip strength compared with placebo [28] which suggests the potential for prebiotic supplementation as a treatment for deficits in age-related muscle function. Similarly, ingestion of a multi-strain probiotic for 12 weeks resulted in significant improvements in physical performance (timed up and go (TUG) test, gait speed) and decreased risk of falls compared with placebo [29].

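### The stated sample-size inputs give about 20 to 36 participants, not 74, so the published power basis is wrong or leaves out a step

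*Protocol article*

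**What the plan says.** All the inputs stand in one paragraph of the Protocol article, under Statistical analyses and power. The estimate "was based on an assumed correlation of 0.7 between the pre- and post-intervention outcome measures". The target effect is Cohen's d = "1.2 for gait speed based on data from" a published probiotic trial with 17 treated and 18 placebo participants. The error rates are given as "To have a power of 80% and a significance level of 5" per cent. The result is that "our study aims to enrol an estimated sample size of 74 participants (37 per group"), and this figure is reached "taking into account a conservative ~ 30% dropout rate".

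The Study intervention section gives 1:1 allocation, and Study design calls the trial a superiority study. The power paragraph does not give the number of completers needed before dropout, whether the test is one- or two-sided, the scale on which d is standardised, or any division of alpha between outcomes. Three measures are headed as primary outcomes (SPPB, handgrip strength, TUG), and Hypotheses and study endpoints lists five primary hypotheses. The analysis text that follows places all tests under Benjamini-Hochberg control of the false discovery rate.

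**The concern.** An effect of 1.2 standard deviations is very large and needs few participants. A pre-post correlation of 0.7 lowers the number further if it is used. A total of 74 therefore looks too big for these inputs, and dropout of 30% cannot make up the gap.

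What is at stake is how the result is read. The paragraph presents d = 1.2 as the effect that the trial detects with 80% power. If 74 gives that power for a much smaller effect, readers are misinformed about the trial's sensitivity, and nobody can check the calculation from what is printed.

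**Working it through.** **Inputs**, all from Statistical analyses and power unless noted: d = 1.2; r = 0.7; power 80%; alpha 5%, taken as two-sided because sidedness is not stated; dropout 30%; 1:1 allocation (Study intervention); stated result 37 per arm.

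**Step 1: try to reproduce 37 per arm.** The normal approximation is n per arm = 2(1.960 + 0.842)² / d², which gives 15.70 / 1.44 = 10.9 for d = 1.2. The t-based calculation gives 11.9. If the correlation is used, d is divided by √(2(1 − 0.7)) = 0.775 for change scores, or by √(1 − 0.7²) = 0.714 for a baseline-adjusted comparison. Dropout is applied as n / 0.7.

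| Analysis | Effective d | Completers per arm (t-based) | Per arm after dropout | Total |
|---|---|---|---|---|
| Final score | 1.20 | 11.9, so 12 | 17.1, so 18 | 36 |
| Change score | 1.55 | 7.6, so 8 | 11.4, so 12 | 24 |
| Baseline-adjusted | 1.68 | 6.7, so 7 | 10.0 | 20 |

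The largest of these is about half of 74. Other variants do not close the gap. One-sided tests give at most 30 in total. Repeated-measures F-tests with f = d/2 = 0.6, two to four time points and r = 0.7 give 9 to 32.

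**Step 2: allow for a different scale for d.** If 1.2 is standardised by the SD of change, the effect in raw SD units is 1.2 × 0.775 = 0.93. At 5% and 80% this needs 19.2, so 20 per arm, and 58 in total. Other conversions (d = 0.86 or 0.84) give at most 70. None reaches 74 at the stated alpha and power.

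**Step 3: see what does give 37 per arm.** The stated figure implies 37 × 0.7 = 25.9, or 26 completers per arm. At least three sets of inputs lead there, each with 26 / 0.7 = 37.1:
- d = 0.8, 5%, 80%, correlation not used: 25.5, so 26.
- d = 0.93, alpha 0.05/3 = 0.0167, 80%: 25.7, so 26.
- d = 0.93, 5%, 90% power: 25.3, so 26.

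The article states none of these.

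**Step 4: what 26 completers per arm provide.** At d = 1.2 the noncentrality is 1.2 × √(26/2) = 4.33 and the critical value on 50 degrees of freedom is 2.01. Power is 98.9% for final scores and above 99.9% for change scores or with baseline adjustment.

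The effect detectable with 80% power, in raw SD units, depends on the alpha that each test faces:

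| Two-sided alpha | Unadjusted for baseline | Baseline-adjusted (× 0.714) |
|---|---|---|
| 0.05 | 0.79 | 0.57 |
| 0.05/3 = 0.0167 | 0.92 | 0.66 |
| 0.05/5 = 0.01 | 0.98 | 0.70 |

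For change scores at 0.05 the value is 0.79 × 0.775 = 0.61. If the test family is the three or five primary tests, the Benjamini-Hochberg threshold lies between the unadjusted and the Bonferroni value, so the lower rows are upper limits.

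**The case against.** The strongest reply is that the paragraph may be incomplete rather than wrong. It sizes the trial for several main outcomes, and three measures carry a primary-outcome heading. Reading 1.2 as a change-score effect and dividing an overall 5% by three uses every stated input and gives 37 per arm. An overall 5% shared between outcomes would not contradict a stated 5% level. This stands as a possible explanation, but it cannot be confirmed. The article mentions no split, and its multiplicity method is Benjamini-Hochberg, not Bonferroni. Even on this account, the published inputs are not enough to obtain the published number.

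Four stronger readings are tempting but not supported:
- **That 74 was derived from d = 0.8.** The figure fits, but so do the two other routes, and the d = 0.8 route discards both the stated effect and the stated correlation.
- **That the trial is underpowered.** For its stated target the opposite holds: power at d = 1.2 is about 99%, and about 95% even at alpha 0.01.
- **That the trial cannot detect its own meaningful gait-speed change of 0.11 m/s** (section on the SPPB). The article gives no SD. For assumed SDs of 0.15 to 0.30 m/s, baseline-adjusted power with 26 per arm runs from 95% down to 44%, so the question stays open. Sizing on a published effect is also a design choice, not an arithmetic error.
- **That the Background contradicts the effect assumed.** It does cite a review that "found no clear evidence of benefit in physical performance in 5 studies", but the same paragraph goes on to report a prebiotic trial with better handgrip strength and a probiotic trial with better TUG and gait speed.

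Nor would a null result be uninterpretable, since it would be read from its confidence interval.

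**Conclusion.** The point holds as a failure to reproduce. The stated inputs need about 36, 24 or 20 participants, depending on the analysis, against the 74 printed. With 26 completers per arm, 80% power is reached at about 0.79 SD unadjusted or 0.57 SD baseline-adjusted at an unadjusted 5%, not at 1.2. The basis as written is either wrong or lacks a step, and the document does not allow a choice between the two.

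This rests on a two-sided test, equal dropout in both arms, d standardised by the raw between-person SD except where converted, and a comparison of two time points. The planned hierarchical model over several visits would shift the detectable effects somewhat. The upper limits under multiplicity assume a family of three or five primary tests; a wider family could raise them.

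This should be fixed. It misstates the trial's sensitivity, but it changes neither the sample size nor any analysis and leaves no shortage of power for the stated target.

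**What to change.** Keep 74 participants and do one of the following in Statistical analyses and power:

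1. If a step was left out, state what actually gave 37 per arm: the effect size and the SD on which it is standardised, the alpha for each test and its sidedness, the power, how the correlation of 0.7 was used, and the number of completers needed before dropout.
2. Otherwise, remove the claim that 74 follows from d = 1.2 at 80% power. Say instead that 26 completers per arm give 80% power for a difference of 0.79 SD unadjusted, or 0.57 SD with baseline adjustment at r = 0.7, at an unadjusted two-sided 5% level. Give the larger values beside these for the planned multiplicity control: up to about 0.92 and 0.66 for three primary tests, or 0.98 and 0.70 for five, at the Bonferroni limit.

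The cost is a few sentences. No participant, visit or procedure changes.
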